#### Physiological recording using VU AMS

The total physiological stress measurement procedure will include five stages, during which stress indices, including HRV/HR and PEP, will be assessed using the VU-AMS device. The five stages are as follows: baseline, neutral script, recovery-1, traumatic script, and recovery-2. The duration of each stage is 5 min (see Fig. 3, timeline of VU-AMS recording). At the baseline, the participant is seated in a relaxed manner without doing any activities. Similarly, at recovery-1 and recovery-2, the participant can relax, and will be allowed to read provided magazines. At the neutral script stage, the participant will be asked to listen carefully to the script “visiting the national library” for 3 min. This stage lasts for 5 min and will continue to recovery-1 stage lasts for 5 min. In the following stage, participants will be asked to listen carefully to the trauma script and then to re-experience the emotions or feelings associated with trauma events for 3 min. This stage lasts for 5 min. Finally, the last stage of recording is recovery-2 period of 5 min. This process will be conducted directly before (session 1) and after treatment (session 6/last intervention).

**Fig. 3 Fig3:**

Timeline of VU-AMS recording

#### Cortisol assays protocol

Cortisol levels will be determined in saliva using salivette sampling devices by the competitive immunoenzymatic method [37]. This method is used for quantitative determination of cortisol concentration in saliva. The area under the curve concerning for to the ground (AUCg) will be determined, as well as the cortisol awakening response (CAR) [38]. Participants are instructed to collect the first sample immediately after waking up or at 7 am, at 30-min post-waking, at 12.00 pm, and at 8.00 pm. Samples are stored in participants’ freezers until research staff collects them to stores them in a freezer at − 20 °C until taken to the laboratory for assay (maximum storage 6 months).

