**Methods:**

The study includes participants who meet criteria of PTSD of the public psychological services in Jakarta and Bandung, Indonesia. One hundred and ten participants are randomly assigned to either an (1) Eye Movement Desensitization group (*n* = 55) or (2) retrieval-only control group (*n* = 55). Participants are assessed at baseline (T0), post-treatment (T1), 1 month (T2), and at 3 months follow-up (T3). Participants are exposed to a script-driven imagery procedure at T0 and T1. The primary outcome is heart rate variability (HRV) stress reactivity during script-driven imagery. Secondary outcomes include heart rate (HR), pre-ejection period (PEP), saliva cortisol levels, PTSD symptoms, neurocognitive functioning, symptoms of anxiety and depression, perceived stress level, and quality of life.

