### Procedure

#### Screening

The study is open for both clients who are already a patient in one of the participating centers and new patients. Both new, chronic, and recurrent PTSD patients are included, and for all participants, the inclusion criterion is a current DSM-5 diagnosis of PTSD. The candidate participant will be invited to the clinic and asked for oral and written informed consent. Next, the participant will be administered the SCID-5 by a trained assessor. The following self-report questionnaires will also be administrated: sociodemographic questions (i.e. gender, age, ethnic), medical history (i.e. medical intervention, kind of drug consumed), and the PCL-5 (PTSD Checklist for DSM-5) [26]. If a candidate meets the inclusion criteria and none of the exclusion criteria, the participant will be invited to the next step of the baseline assessment after a break of 15 min.

A research assistant will provide information about the purpose of the study, including the background rationale of the study, risks and safety, benefits, and their right to withdraw from the study at any time without consequences. The participants will be asked oral and written informed consent for the RCT before entering the study.

The research assistant will continue the baseline assessment by administering the Hopkins Symptoms Checklist-25 (HSCL-25) [27], the Perceived Stress Scale (PSS [28];), and the World Health Organization Quality of Life (WHOQOL-BREF [29];). Neurocognitive tests administered at baseline include the Trail Making Test (TMT) [30], California Learning Verbal Test (CLVT [31];), and Subtest Digit Span of the Wechsler Adult Intelligence Scale fourth edition (WAIS-IV) [32]. Finally, participants will be instructed on how to collect saliva for cortisol analyses.

The second part of the baseline assessment includes the physiological measurements, using the VU University Ambulatory Monitoring System (VU-AMS) device when the participant listens to the traumatic script. The physiological measurements are performed 1 week after the T0, directly before the first treatment session. The reason is that the traumatic script needed for the physiological measurements will be prepared based on the information gathered at the T0. The recording procedure of VU-AMS is explained in the stress measurement section.

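### The 7 am alternative for the first saliva sample breaks the 30-minute interval that the cortisol awakening response needs, except for someone who wakes at 07:00

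*Protocol article*

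**What the plan says.** The abstract of the protocol article lists cortisol among the secondary outcomes: "Secondary outcomes include heart rate (HR), pre-ejection period (PEP), saliva cortisol levels". The section *Cortisol assays protocol* names two quantities to be derived: "AUCg) will be determined, as well as the cortisol awakening response (CAR"). It then gives four collection times, in order samples 1 to 4. Participants are to "collect the first sample immediately after waking up or at 7 am, at 30-min post-waking, at 12.00 pm, and at 8.00 pm".

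Samples are kept in participants' own freezers until staff collect them, so sampling is done at home. Under *Screening* the article adds only that "participants will be instructed on how to collect saliva for cortisol analyses". Saliva is collected at baseline and again after treatment; it is not in the list for the 1-month and 3-month follow-ups (*Randomization*).

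Nothing in the article says when the 7 am alternative applies or that participants should wake at 7 am.

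**The concern.** An awakening response compares cortisol at waking with cortisol a fixed time later. In this schedule only samples 1 and 2 can supply it, and the intended gap is evidently 30 minutes. The instruction gives sample 1 two possible anchors, waking or the clock, and sample 2 only one. If the clock anchor is used, the gap depends on when the person happened to wake.

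This is a stated sampling rule that conflicts with a stated outcome, which is different from detail left to a fuller document. An analysis plan cannot recover a waking sample that was never taken. Change in the CAR rests on two collections per person, so one mistimed morning is enough to spoil that person's change score.

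**Working it through.** The plan states no figure to reproduce here; the check is clock arithmetic on the schedule.

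**Inputs.** From *Cortisol assays protocol*: S1 = W (waking time) or 07:00; S2 = W + 30 min; S3 = 12:00, reading 12.00 pm as noon; S4 = 20:00. W is not given in the document. The values below are assumed for illustration.

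**CAR interval.** Under the waking option, S2 − S1 = (W + 30 min) − W = 30 min for every W. Under the 7 am option, S2 − S1 = W + 30 min − 07:00:

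| W | S1 | S2 | S2 − S1 |
|---|---|---|---|
| 05:00 | 07:00 | 05:30 | −90 min |
| 05:30 | 07:00 | 06:00 | −60 min |
| 06:00 | 07:00 | 06:30 | −30 min |
| 06:30 | 07:00 | 07:00 | 0 min |
| 06:45 | 07:00 | 07:15 | +15 min |
| 07:00 | 07:00 | 07:30 | +30 min |

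For W after 07:00, a 07:00 sample would fall before natural waking. So under the 7 am option only W = 07:00 gives the intended gap. At W = 06:30 both samples fall at the same moment and no response can be measured. For earlier waking the post-waking sample precedes the nominal first sample.

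**AUCg span, all participants sampling at waking.** Span = 20:00 − W: 15 h at 05:00, 14 h at 06:00, 13 h at 07:00, 12 h at 08:00. At a constant cortisol level the area is proportional to the span, so 05:00 against 08:00 gives 15/12 = 1.25. With one assumed set of concentrations (10, 15, 6, 3 in sample order) the trapezoid areas are:

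- W = 05:00: 0.5 × 12.5 + 6.5 × 10.5 + 8 × 4.5 = 110.5
- W = 08:00: 0.5 × 12.5 + 3.5 × 10.5 + 8 × 4.5 = 79.0

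The four measured values are identical and the areas differ. The 7 am option plays no part in this comparison.

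**What the 7 am option itself does to the span, at a fixed waking time.** For W at or before 06:30 the earliest sample under the option is S2 = W + 30 min, so the span is 30 minutes shorter than under the waking option. At W = 05:30: 14.5 h against 14 h, 14.5/14 = 1.036. At W = 06:30: 13.5 h against 13 h, 13.5/13 = 1.038. That is about 4%.

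**The case against.** **7 am may simply be the expected waking time.** If so, the interval is exactly 30 minutes. The order of the list also suggests that the waking or 7 am tube comes first, so a reversed pair requires someone to take the later-listed sample before the earlier one. This is a fair reading, but the text does not say it, and a participant at home can take the alternative as a free choice. The zero and negative intervals are what the rule permits, not what is known to have happened. Use of different options before and after treatment is likewise possible but undocumented.

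**Separate collection instructions exist.** The article says participants are instructed, and time logs, acceptance windows and missing-sample rules usually sit in a fuller document. Their absence from a journal article is no fault. The conflict in the stated sampling times remains.

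**A reader might infer that the 7 am option is what makes AUCg spans unequal**, for instance by setting 14.5 h from 05:30 against 13 h from 07:00 (14.5/13 = 1.115, about 12%). The schedule does not support this. That ratio compares two waking times and does not isolate the option. Someone who wakes at 05:30 and uses 7 am still gives a sample at 06:00, so the collected samples span 14 h, not 13 h. At a fixed waking time the option accounts for about 4% in the two cases above. The unequal spans come mainly from a first sample tied to waking and a last sample tied to 20:00.

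**The stakes are limited.** Cortisol is one of many secondary outcomes, while the primary outcome is RMSSD in response to the trauma script and the sample size rests on HRV. Randomization makes a systematic difference in sampling times between arms unlikely. All of this stands.

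**Conclusion.** The instruction is wrong as written for the CAR. Under the 7 am option it yields the 30-minute interval for one waking time only, a zero interval at 06:30, and a negative one before that. Such values should not be analysed as awakening responses.

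The conclusion rests on a literal reading of the alternative and on the CAR being taken from samples 1 and 2. With no waking times and no record of how often the option was used, the share of participants affected cannot be computed. The expected effect is added measurement error in one of two cortisol summaries. Neither bias between arms nor any effect on the primary HRV analysis follows from it.

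The AUCg issue is separate. Among participants who sample at waking, spans differ with waking time (15 h against 12 h in the example), and removing the 7 am option leaves that in place.

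**What to change.** 1. Delete the 7 am alternative, so that sample 1 is taken at waking and sample 2 is taken 30 minutes later. Have participants record the waking time and each sampling time.
2. Do not compute a CAR, and set it to missing, where sample 1 is known not to have been taken at waking. Apply this also to samples already collected under the 7 am option; recruitment began on 21 April 2019, so there may be some. Where times were not recorded this cannot be checked, and the report should state it as a limitation of the CAR.
3. Compute AUCg from actual sampling times and either divide by the span or use a window common to all participants. Dividing turns the area into a mean level over the sampled period, so say so when reporting it. In the illustration it narrows the gap without closing it: 110.5/15 = 7.37 against 79.0/12 = 6.58.

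The cost is one line in the participant instruction, a place to write times, and a few missing CAR values. For samples already collected without recorded times, nothing beyond the stated limitation can be recovered.

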### Outcome measures

#### Primary outcome

The primary outcome of this study is the level of the HRV in response to the trauma script. HRV is an indicator of the activity of the parasympathetic nervous system, which is active in resting conditions. HRV represents the change in the time interval between successive heartbeats [21]. The time between beats is measured in milliseconds (ms) and is called an R-R interval or inter-beat interval (IBI). Time domain analyses measures the changes in heart rate over time or the intervals between successive normal cardiac cycles. We will use root mean square of the successive differences (RMSSD) as the outcome metric for the primary outcome. RMSSD is one of a few time-domain tools used to assess HRV, the successive differences being neighboring RR intervals [39]. Kim and Woo found that normal range of RMSSD in population was 29.7 ± 18.1 ms [40]. In this study, we expect that there is a difference in the change of HRV (Δ HRV) between the experimental and the control group (Δ HRV in the experimental group is smaller than Δ HRV in the control group). HRV will be measured at time point T0 (baseline) and T1 (post-treatment) for all participants.

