In addition, only a few studies examined whether EMDR improves stress reactivity related to traumatic memory retrieval as part of the arousal and activity cluster of symptoms in PTSD [14]. Stress reactivity is defined as the reactivity of the autonomic nervous system, which is represented by decreased heart rate variability (HRV) and decreased pre-ejection period (PEP), and increased heart rate (HR) in response to a trauma-related stressor [15]. It has been suggested that EMs in EMDR are beneficial and have a distinct effect on psychophysiological responding [16]. The orienting response theory of EMDR states that EMs, or other dual-attention stimuli, elicit an orienting response with associated physiological de-arousal that enhances trauma material processing [17]. The previous studies in non-clinical and clinical participants have found that EMDR led to significant reductions in heart rate and skin conductance responses to trauma recall compared to a relaxed state [16, 18].

Therefore, it is important to examine whether EMD is associated with reduced stress reactivity among clinical PTSD patients. Psychophysiological stress mechanisms that may play a role in PTSD treatment effects include reduced physiological stress reactivity, assessed with heart rate (HR) and heart rate variability (HRV) responses, and neuroendocrine stress response, as indexed by cortisol levels in saliva [19, 20]. HRV represents the change in the time interval between successive heartbeats. HRV provides an index of the parasympathetic nervous system and has been associated with emotional self-regulation [21].

Besides activating autonomic functioning, stress also activates the hypothalamic-pituitary adrenal (HPA) axis. Activation of the HPA axis is indexed by heightened cortisol levels. High levels of saliva cortisol have been associated with general life stress and emotional regulation that influences cognitive function [22, 23].

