A previous study has found a significant relationship between PTSD symptoms and neurocognitive deficits, suggesting that PTSD symptoms may also interfere with executive function and may cause impairments in cognitive flexibility [24]. Another study showed that improved neurocognitive functioning might be a potential mechanism for long-term maintenance of treatment gains following CBT for PTSD [25]. This study will focus on specific elements of neurocognitive functioning, including memory, attention, and information processing, and examine whether these indices improve after EMD.

If we find evidence for reduced stress reactivity and improved neurocognitive functioning after EMD, it can help in understanding part of the underlying mechanisms through which EMD exerts its effects on PTSD symptom reduction. To examine this, we will compare EMD with a control condition, consisting of the same procedure as EMD, but without the EM. Furthermore, we will investigate whether PTSD symptom reduction is related to reduced stress reactivity and neurocognitive functioning. We hypothesize that participants with PTSD receiving the EMD condition will show larger stress reactivity reductions in response to trauma scripts and greater improvements in neurocognitive functioning than the retrieval-only control group.

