#### Sample size

We expect that HRV will decrease in both groups at T1 compared with T0, with a smaller decrease in the EMD group, resulting in greater HRV at T1 in the EMD group compared with the EMD retrieval-only control group. No studies have been carried out yet comparing the effect of EMD to retrieval only on HRV in PTSD patients to inform power calculations. However, based on the theoretical assumptions and studies with other related outcome measures [63, 64], we expect to detect a difference between the EMD condition and retrieval only on HRV of a medium effect size (Cohen’s *d* = 0.4). Power calculations were conducted using G*power software and were based on based on a general linear model (GLM). Linear mixed-effect model can be conceptualized as GLM (repeated measure ANOVA) as a balanced design within independent sampling units, and an unstructured covariance model is assumed [65]. We transformed for Cohen’s *d* = 0.4 into *f* = 0.2. For a 2 between (treatment EMD conditions) X 2 within (baseline, post-treatment) repeated measure ANOVA (*α* = 0.05, power = 0.9, correlation between measures = 0.4, and medium effect-size *f* = 0.2) [7, 66]. A power calculation suggested that a total sample size of *N* = 82 will be required, which is 41 per condition. All power computations were conducted in the G*Power software. Considering drop out of participants, we will recruit an additional 25% extra participants, yielding a total number of 55 participants per condition, thus 110 participants in total.

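### The primary outcome is called HRV stress reactivity but defined as the HRV level during the trauma script, so the planned test cannot separate reactivity from resting HRV; Δ HRV is also undefined

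*Protocol article*

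**What the plan says.** On the construct:

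- Protocol article, abstract (Methods): "The primary outcome is heart rate variability (HRV) stress reactivity during script-driven imagery".
- Background: stress reactivity is represented by "decreased heart rate variability (HRV) and decreased pre-ejection period (PEP), and increased heart rate (HR) in response to a trauma-related stressor". This describes a response to a stressor, and the Objective makes reducing it the aim of the trial.
- Primary outcome: "The primary outcome of this study is the level of the HRV in response to the trauma script", with RMSSD as the metric. The sections on heart rate and pre-ejection period likewise take the level under the trauma script.
- Physiological recording using VU AMS: each session has five stages of 5 minutes, namely "baseline, neutral script, recovery-1, traumatic script, and recovery-2".
- Statistical analysis: repeated measures ANOVA with time (T0, T1) and treatment group, adjusted for age, gender and type of trauma. Stage is not a factor, and no resting or neutral-script value is a covariate.

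On the direction:

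- Background: EMD participants "will show larger stress reactivity reductions in response to trauma scripts" than controls.
- Primary outcome: "Δ HRV in the experimental group is smaller than Δ HRV in the control group".
- Sample size: "We expect that HRV will decrease in both groups at T1 compared with T0, with a smaller decrease in the EMD group". The sentence ends by expecting higher HRV at T1 under EMD than under retrieval-only.

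**The concern.** Reactivity is the difference between a stressed state and a reference state. The level during the trauma script is the sum of the resting level and the script-induced change. The protocol records the reference stages, but the stated outcome and model leave them out. A treatment that altered resting vagal tone alone would move the primary outcome. A treatment that altered reactivity while resting tone moved the other way could leave it unchanged. Either result would be read as an answer about reactivity, which is the trial's stated question.

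The wording of the expected effect adds a second problem. Δ could be a change over time or a change between stages, signed or as a magnitude, and these readings do not agree with each other or with the hypothesis. With construct and Δ both open, more than one primary analysis could be chosen after the data are seen.

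**Working it through.** **1. The plan's own sample size.** Inputs from the Sample size section: f = 0.2, correlation between measures ρ = 0.4, α = 0.05, power 0.9, two groups, m = 2 occasions. For the within-between interaction, λ = N·f²·m/(1 − ρ) with 1 and N − 2 degrees of freedom. At N = 82, λ = 82 × 0.04 × 2/0.6 = 10.93 and power is 0.904; at N = 80 power is 0.897. So N = 82 reproduces. With 25% dropout, 82/0.75 = 109.3, rounded up to 110, which also reproduces. The problem here is the variable being tested, not this arithmetic. Whether f = 0.2 is the right translation of d = 0.4 is a separate question.

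**2. Level against reactivity.** Take the population SD of 18.1 ms quoted in the Primary outcome section and, for illustration only, a shift of 0.4 SD: 0.4 × 18.1 = 7.24 ms. The table gives the extra T0-to-T1 change under EMD compared with control.

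| Assumed scenario | Rest | Trauma script | Level interaction | Reactivity interaction (script − rest) |
|---|---|---|---|---|
| Equal rise in both stages | +7.24 | +7.24 | 7.24 | 7.24 − 7.24 = 0 |
| Resting level falls, script level unchanged | −7.24 | 0 | 0 | 0 − (−7.24) = 7.24 |

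The two outcomes can disagree completely, in either direction. (On a log scale the equivalent of the first row is an equal proportional shift.)

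**3. Direction.** By the Background definition, reduced reactivity means a smaller script-induced fall in HRV. If resting HRV is stable, script HRV then rises from T0 to T1, more so under EMD. Suppose, in line with the Sample size section, that HRV changes by −2 ms under EMD and −6 ms under control. There are three readings of Δ:

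- *Signed T1 − T0 of the script level.* −2 is larger than −6, so Δ is larger under EMD. The Primary outcome section would then be reversed relative to both the Sample size section and the hypothesis.
- *Size of the fall from T0 to T1.* 2 is less than 6, so the Primary outcome and Sample size sections agree. But both arms then move towards lower HRV during the script, which does not fit reduced reactivity unless resting HRV is expected to fall further still. The article does not say so.
- *Resting minus script HRV within a session.* A smaller Δ under EMD agrees with the hypothesis, but this is neither the level named as the outcome nor the T0-to-T1 change used for the sample size.

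No single reading fits the Background, Primary outcome and Sample size sections together.

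**4. What a contrast would do to power.** The article gives no T0–T1 correlation for a reactivity score. Keeping f = 0.2 and the formula in step 1, with ρ as an assumed range:

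| ρ | N for 90% power | Power at N = 82 |
|---|---|---|
| 0.2 | 108 | 0.81 |
| 0.3 | 94 | 0.86 |
| 0.4 | 82 | 0.90 |
| 0.5 | 68 | 0.95 |
| 0.6 | 56 | 0.98 |

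Keeping f assumes the same effect in units of the contrast's own SD. If two stages each had SD 18.1 ms and within-session correlation r, the contrast SD would be 18.1 × √(2(1 − r)): 18.1 ms at r = 0.5, 11.4 ms at r = 0.8 and 8.1 ms at r = 0.9. The contrast is noisier than the level only if r is below 0.5.

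**The case against.** The strongest defence is that the article is condensed. Its phrase about HRV in response to the script may intend a contrast, the script-driven imagery section plans to measure responses to neutral as well as traumatic stimuli, and scoring of the five stages is commonly left to an analysis plan. This explains how the wording may have arisen. It does not remove the conflict, because the article does not leave the matter open: it names a level and fixes a two-factor model without stage.

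Three stronger readings are tempting, and the documents do not support them.

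- *That the analysis cannot show reduced reactivity at all.* This goes too far. The F test is non-directional and valid for the level, and a genuine fall in reactivity with stable resting HRV would appear in it. The limitation is that the test cannot tell this apart from a tonic change.
- *That harm could be labelled as benefit.* The Sample size sentence ends by expecting greater HRV at T1 under EMD, and the Background links lower HRV to stress reactivity, so the favourable between-arm direction can be inferred. The Δ statement is ambiguous rather than plainly reversed.
- *That a rate of false reactivity findings can be quoted.* Any such rate is only the power of the level test under an assumed, purely tonic effect, and nothing in the article supports that scenario. Nor is the population figure of 29.7 ± 18.1 ms a basis for claims about skewness or lost efficiency in these patients.

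**Conclusion.** The point holds in a limited form. The primary outcome is described in two non-equivalent ways, and the version carried into the analysis cannot distinguish altered reactivity from altered resting HRV. The same applies to heart rate and pre-ejection period. The possible discrepancy is as large as the effect itself: in the worked example, 7.24 ms on one definition and 0 on the other. That example rests on an assumed shift and a population SD, so it shows that the definitions can diverge, not how often they will.

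On direction, Δ HRV is undefined, and the expected fall in both arms does not fit the hypothesis unless something unstated is assumed about resting HRV. This leaves the validity of the p-value intact, but it leaves the meaning of the primary result unsettled.

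**What to change.** 1. Define one primary variable per session: RMSSD in the trauma-script stage relative to one pre-specified stage of the same session. Neutral script or resting baseline is defensible, but only one should be named. A log scale is a reasonable option, not a requirement.
2. Compare arms on this variable at T1, adjusted for its T0 value.
3. Treat heart rate and pre-ejection period in the same way. Keep the trauma-stage and resting levels as secondary outcomes, so that a tonic change can be seen and named as such.
4. Define Δ by stage, time point and order of subtraction, and state one signed hypothesis: the script-induced fall in HRV at T1 is smaller under EMD than under retrieval-only. Align the abstract, Background, outcome sections, Sample size and Statistical analysis with it.

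No new measurement is needed, since all five stages are already recorded. The change is still more than rewording. It alters the primary variable and model of a registered trial that is already recruiting, so it should be a dated amendment made before allocation is revealed to the analyst. A contrast may be noisier than a level, and f = 0.2 and ρ = 0.4 must be justified afresh for it. At the low end of the assumed range (ρ = 0.2), 90% power would need 108 completers, or 108/0.75 = 144 recruited at the plan's 25% dropout, against the planned 110.
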